### Patient Selection, Recruitment, Randomization, and Blinding

#### Eligibility

Eligibility will be determined based on the inclusion and exclusion criteria listed in Table 2. Eligible participants will be identified after initial evaluation by a staff ophthalmologist, determined to satisfy 1 of the qualifying procedures, and approached for informed consent by the ophthalmologist and research staff. At this time, patients will watch an introductory video explaining the purpose of the clinical trial. The physician also will lead an in-depth preintervention discussion explaining each approach to stress and sleep disability (SWL and OM vs control) and postintervention expectations. If patients decline to participate in the RCT, they will be presented with the option of enrolling in the control group (no intervention). There will be no restrictions on patient care due to enrollment in the study.

**Table 2 table2:** Inclusion and exclusion criteria at screening.

Inclusion criteria	Exclusion criteria
Age 18-65 years, from ReCYL^a^ Diagnosis of moderate or severe RP^b^ (grading severity scale score>1 point) Visual function enough to tolerate and see through the optic filters during daily activities Written informed consent provided	Underwent any ocular surgery within the previous 6 months Involvement in any other ongoing clinical trial Pregnancy and lactation or under hormonal treatment Allergy or hypersensitivity to melatonin Previous or current therapy with melatonin Autoimmune diseases NSAID^c^ and others anti-inflammatory drug treatment Psychiatric disorders or under any psychotropic medication

^a^ReCYL: Retina Castilla y León.

^b^RP: retinitis pigmentosa.

^c^NSAID: nonsteroidal anti-inflammatory drug.

#### Recruitment

##### Screening Visit

Patients will undergo an initial screening visit that includes a semistructured interview, a series of questionnaires, a complete ophthalmic examination, and laboratory assessment. Eligible patients will be provided with a verbal description of the trial and presented with a comprehensible informed consent form.

##### Semistructured Interview

All patients will undergo a semistructured interview to collect medical (signs and symptoms, personal and family records, coexisting pathology, previous or current medication, etc), demographic (age, gender, ethnicity, etc), socioeconomic (relationship status, educational attainment, employment status, etc), and lifestyle (physical exercise, consumption of drugs, use of hair dyes, BMI, etc) data.

##### Ophthalmic Examination

All patients will undergo a complete ophthalmological examination, which will include the best-corrected visual acuity (BCVA) with the Early Treatment of Diabetic Retinopathy Study (ETDRS) letter score, a slit lamp examination, intraocular pressure measurement, fundoscopy, contrast sensitivity with a CSV-1000 chart (Vectorvision), and a glare test with the MonPack 3 device (Metrovision).

##### Ancillary Tests

Visual field impairment (VFI) will be assessed using a Humphrey 750i visual field analyzer (Carl Zeiss) and the central 30-2 SITA fast strategy protocol. Only tests that met the criteria (low [<20%], false positive, false negative, and fixation loss parameters) were evaluated [84].

Optical coherence tomography (OCT) images, assessing the central retinal thickness (CRT), macular ganglion cell–inner plexiform layer (GCIPL) thickness, and retinal nerve fiber layer (RNFL), will be performed using Cirrus HD-OCT 5000 with AngioPlex OCT-A (Carl Zeiss Meditec V.10.0) and cube scans. Only images with a signal strength of >6 with no movement artifact will be included in the study.

Two consecutive optical coherence tomography angiography (OCTA) images will be obtained by a single skilled examiner. A foveal centered scan area of a 3×3 mm^2^ pattern will be used, and all scans will be analyzed using en face OCTA images generated automatically with the optical coherence tomography microangiography (OMAG) algorithm in Angioplex software (ZEISS). The foveal avascular zone (FAZ) area will be manually outlined and expressed as square millimeters.

The vascular density (VD) will be measured automatically by the software, which will quantify the VD of a local region of tissue according to the ETDRS subfields. We will analyze the VD of each ETDRS sector, the inner ring, and the full area in 3×3 mm^2^ rings and exclude OCTA images with a signal strength of <7 [12].

The axial length will be calculated using an IOLMaster 500 optical biometer (Carl Zeiss Meditec) to be used as a correcting variable in the analysis, if necessary.

##### Questionnaires and Diaries

The State-Trait Anxiety Inventory (STAI), the Epworth Sleepiness Scale (ESS), the Pittsburgh Sleep Quality Index (PSQI) questionnaires and a sleep diary will be used to ask patients about their level of sleep quality, perceived stress, and anxiety.

##### Sleep Diary

During the 2-week period before trial commencement and the 4-week period of the intervention, patients will fill a daily self-recorded sleep diary at home. The sleep diary will record parameters such as bedtime, wake time, sleep onset, and sleep offset time.

##### State-Trait Anxiety Inventory

STAI is designed to assess the degree of state and trait anxiety in research participants (in this study, patients with moderate and severe RP) and takes about 10 minutes to complete. It is a reliable, valid, and responsive questionnaire consisting of 20 items for assessing state anxiety and 20 for trait anxiety. Higher scores (maximum score of 40) are positively correlated with higher levels of anxiety [85]. To evaluate the magnitude of any treatment effect, the minimum clinically important difference (MCID) will be regarded as a 30% reduction from baseline [86]. This magnitude represents a “small” effect in the behavioral sciences.

##### Epworth Sleepiness Scale and Pittsburgh Sleep Quality Index

The ESS and the PSQI are both sleep quality questionnaires. The ESS is widely used in the field of sleep medicine as a subjective measure of a patient’s sleepiness. The overall score ranges from 0 to 24. The scale estimates whether the patient is experiencing excessive sleepiness that possibly requires medical attention [87]. The PSQI is a self-reporting questionnaire that assesses sleep quality over a 1-month time interval. The global PSQI score is calculated by adding the 7 component scores, providing an overall score ranging from 0 to 21, where lower scores denote a healthier sleep quality [88].

As determination of the MCID in the sleep quality questionnaires remains controversial, with no consensus on methodology, we will estimate the minimum clinically important improvement in the ESS and PSQI to lie between −2 and −3 for this trial [88-92].

##### Laboratory Assessment

All patients will undergo a salivary and hair draw to confirm eligibility. Sample collection will be carried out between 9:00 A.M. and noon to minimize potential errors associated with diurnal variations in neuroendocrine parameters. Samples will be collected in the same room, and temperature and humidity will be recorded. After collection, samples will be frozen at –20 °C until analysis. When analyzing results, in female subjects, menstrual cycle phases will be considered.

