The aim of this study is to assess the efficacy of OM combined with SWL-blocking filters in patients with RP who have sleep disorders and stress compared to any intervention alone or no intervention. We hypothesized that both interventions would improve their sleep quality, reduce their perceived stress levels, and shift their circadian rhythm to morningness.

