##### Salivary α-Amylase, Cortisol, and Melatonin levels

Salivary samples will be collected by patients using the passive secretion drooling method. Two samples of saliva from each patient will be collected in 24 hours. At least 1 mL is required for analysis. The putative salivary indicators will be assayed with enzyme-linked immunosorbent assay (ELISA): cortisol (DRG Salivary Cortisol ELISA, DRG Instruments GmbH) and melatonin (DRG Instruments GmbH). Salivary α-amylase (sAA) will be determined with an α-amylase kit (Salimetrics) [93].

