### Data Collection and Outcome Measures

#### Baseline Assessments and Frequency of Follow-Up Assessments

A full list of assessments obtained at each time point is summarized in Table 3.

We will obtain baseline assessments during each patient’s screening visit. These measures will include, but will be not limited to, demographics, comorbidities, subjective sleep quality and perceived stress rating, ophthalmic and laboratory outcomes, and patient-reported outcomes specific to the planned intervention.

Initial follow-up assessments will be obtained at 1, 2, 3, and 4 weeks after the start of the intervention. Patients will also be asked to return for postintervention follow-up visits 6 months after the intervention. These visits will be scheduled at the beginning of the study. Patients unable to attend any in-person visit will be asked to at least provide all subjective patient-reported outcomes over the phone or via an electronic survey for that visit in order to facilitate retention and optimal follow-up.

Sleep quality level, laboratory outcomes, ophthalmic clinical outcomes, questionnaire patient-reported outcomes, and potential complications will be gathered during these visits.

**Table 3 table3:** Assessments and follow-up.

Clinical and laboratory event	V_–1_^a^ (–4 weeks)	V_0_ (0 weeks)	V_1_ (1 weeks)	V_2_ (2 weeks)	V_3_ (3 weeks)	V_4_ (4 weeks)	V_F_ (6 months)
Screening	✓^b^	—^c^	—	—	—	—	—
Clinical	—	✓	—	—	—	✓	✓
Physical examination	—	✓	—	—	—	✓	✓
Salivary sample collection	—	✓	✓	✓	✓	✓	—
Hair sample collection	—	✓	—	—	—	✓	—
STAI^d^ questionnaire	—	✓	—	—	—	✓	—
ESS^e^ and PSQI^f^ questionnaires	—	✓	—	—	—	✓	—
Inclusion criteria	✓	—	—	—	—	—	—

^a^V: visit; V_–1_, screening visit, when inclusion and exclusion criteria will be checked; V_0_, visit to assess baseline characteristics; V_1_-V_4_, visits during the intervention period (every week); and V_F_, final visit after 6-month follow-up.

^b^✓: applicable.

^c^Not applicable.

^d^STAI: State-Trait Anxiety Inventory.

^e^ESS: Epworth Sleepiness Scale.

^f^PSQI: Pittsburgh Sleep Quality Index.

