#### Primary Outcome Measures

The primary outcomes are the differences in changes from baseline to postintervention in hormone release (sAA, cortisol, and melatonin levels in salivary and hair samples) and sleep quality, as measured by the ESS and the PSQI.

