We have selected melatonin as an intervention because of its close relationship with and involvement in the regulation of circadian cycles and its antioxidant and anti-inflammatory potential.

Melatonin’s functions are either receptor dependent or receptor independent. The former includes circadian rhythm control and sleep regulation. There is a considerable body of evidence of melatonin regulating sleep in various sleep disorders [7,62-66]. In fact, melatonin appears as one of the most effective drugs for treating circadian rhythm sleep-wake disorders [67]. Aging, the presence of certain diseases (eg, primary degeneration of the autonomous nervous system and diabetic neuropathy, some types of neoplasms, Alzheimer disease), and certain drugs (eg, β-blockers, clonidine, naloxone, and NSAIDs) abolish the nocturnal production of melatonin and are associated with impaired sleep [7,61,79,81].

Melatonin acts via its own receptors (MT1, MT2) present at the SCN, which are members of the G protein–linked receptor family [61]. The phase-shifting effects of melatonin are essentially opposite to those of light. In humans, its sleep-promoting effects become significant about 2 hours after intake, similar to the physiological sequence at night. However, administration of melatonin during the daytime (when its endogenous levels are minimal) results in induction of fatigue and sleepiness in humans [79,81].

Thus, melatonin administration appears to be one of the most promising approaches, with long-term benefits, for circadian rhythm sleep disorders because it simultaneously treats sleep and wake state problems and, in addition, synchronizes other bodily rhythms so as to maintain the body’s internal temporal order and prevent internal desynchronization [67,79,81].

Although the receptor-independent functions of melatonin include the detoxification of ROS and other reactive molecules, the antioxidant action of melatonin can also be expressed by increasing the efficacy in preventing oxidative DNA damage [7,51,58,60,61].

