Accumulating evidence indicates that melatonin has a protective effect against various ocular disorders, such as uveitis, diabetic retinopathy, glaucoma, and even optic neuritis, through different mechanisms of action [60,61,73,112-115]. The multifaceted role of melatonin in neuroprotection might imply that melatonin may possess the capacity to attenuate the harmful effects that occur in degenerative retinal diseases, such as RP. Daily administration of melatonin has been shown to delay the photoreceptor apoptotic loss in RP mice [53,116]. This evidence supports that a clinical trial using melatonin to at least delay cell loss in RP in humans might be beneficial. In this context, a Spanish RCT (EudraCT no: 2012-002436-82) with 6 mg of OM and patients with RP is ongoing. Thus, therapeutic treatments of eye diseases using melatonin alone or in combination with other strategies deserve serious investigation.

The possibility of synergy between the 2 strategies stems from the common point between them—their involvement in circadian rhythms. Glucocorticoid hormones, particularly cortisol, participate in the body’s homeostasis and stress responses and follow a circadian rhythm, exhibiting a predictable peak in the morning, with a typically sharp elevation 30 minutes to an hour after awakening [117-119], although one that is apparently more complex than the melatonin rhythm.

The sAA enzyme has been used as a marker for the sympathetic nervous system response [118,120,121] and, like cortisol, has been shown to respond to psychosocial stress [118]. As with melatonin and cortisol, sAA production exhibits a regular circadian pattern [118]. Under normal, steady-state conditions, high levels of cortisol tend to be associated with low levels of sAA and vice versa.

Synthesis of melatonin is affected by SWL, whereas cortisol production and sAA levels are modulated by both short- and long-wavelength light. Since light is a well-known stimulus for suppressing the synthesis of the hormone melatonin at night, it was considered important for this study to also understand how blocking SWL in bright-light conditions may prevent the suppression of melatonin, which could affect perceived stress, sleep quality, and the quality of life of patients with RP.

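### Salivary melatonin is a primary outcome, but the only stated collection window is 9:00 A.M. to noon, which is poorly placed to show a night-time effect

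*Protocol article*

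**What the plan says.** - **Primary Outcome Measures** lists changes from baseline in "hormone release (sAA, cortisol, and melatonin levels in salivary and hair samples"), together with two sleep questionnaires. The hair section describes a cortisol assay only, so saliva is the only described source of melatonin data.
- **Laboratory Assessment** sets the time: "Sample collection will be carried out between 9:00 A.M. and noon to minimize potential errors associated with diurnal variations in neuroendocrine parameters". It adds: "Samples will be collected in the same room, and temperature and humidity will be recorded". No exception is made for melatonin.
- **Salivary α-Amylase, Cortisol, and Melatonin levels** says: "Two samples of saliva from each patient will be collected in 24 hours". It gives no clock time for either sample.
- **Table 3** ticks the row "Salivary sample collection" at V0 to V4, also without clock times.
- **Summary of Findings** (Discussion) refers to "administration of melatonin during the daytime (when its endogenous levels are minimal"), and introduces the melatonin rationale with "Since light is a well-known stimulus for suppressing the synthesis of the hormone melatonin at night".
- **Optical Filters for Blocking SWL** gives prevention of melatonin suppression as the purpose of the goggles. **Background and Rationale** hypothesises that the interventions will "shift their circadian rhythm to morningness".

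**The concern.** The sampling window was chosen to remove diurnal noise. That suits cortisol and α-amylase. Melatonin differs because the quantity of interest is itself the night-time part of the diurnal pattern. Holding the clock time in the morning keeps the measurement near what the protocol calls the hormone's low point, away from the hours when light is said to suppress it.

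The interpretation of one primary outcome is at stake. If the filter and control arms do not differ on morning melatonin, the trial could not tell an ineffective filter from a sample taken at an uninformative hour. A later analysis plan cannot repair this, because it cannot recover samples that were never taken.

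**Working it through.** The protocol gives no figure to reproduce here. The check is clock arithmetic and a comparison of sections.

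**1. Coverage of the day.** The window is 9:00 to 12:00, so 3 h / 24 h = 12.5% of the day, all of it in daytime. No evening or night time for saliva is stated anywhere.

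**2. Position relative to the oral dose (melatonin arms).** Intake is at 22:00 with 30 minutes either side, so between 21:30 and 22:30.
- Shortest gap: 22:30 to 9:00 = 1.5 + 9 = 10.5 h.
- Longest gap: 21:30 to 12:00 = 2.5 + 12 = 14.5 h.

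The Discussion mentions a short plasma half-life but gives no value. How much ingested melatonin remains at sampling therefore cannot be calculated. I assume the assay would not separate ingested from endogenous hormone; the document does not say.

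**3. What the two samples in 24 hours can be.**

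| Reading | Consequence |
|---|---|
| Both follow the 9:00 to noon rule (same or consecutive mornings) | No evening or night melatonin value exists |
| One is meant for evening or night | It contradicts the stated window, and the two sections must be reconciled |

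**4. Purpose against measurement.** The Discussion locates the light effect on melatonin at night and calls daytime levels minimal. The primary outcome rests on saliva. The only sampling hours given are daytime hours. Followed as written, the plan measures melatonin where its own text expects the least of it.

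**5. An evening sample for comparison.** A sample taken just before 21:30 follows the previous evening's dose (21:30 to 22:30) by about 23 to 24 h, against 10.5 to 14.5 h for a morning sample. It lies closer to the hypothesised effect and leaves less room for carry-over of the ingested hormone.

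**The case against.** **The window may apply to screening only.** Laboratory Assessment does sit under Recruitment and opens with confirming eligibility. But if its rule stops there, no clock time governs the saliva at V0 to V4, and an uncontrolled hour would enter the change from baseline. That does not rescue the outcome.

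**The two samples may include an evening one.** The wording allows it, and a condensed article may leave such detail to the full protocol. What the article does state is a morning window without exception, so an evening sample would contradict it.

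**These patients may not be at their trough in the morning.** This has force. The Introduction describes people with eye disease and blindness whose clocks are not synchronised to the 24-hour day. In them morning melatonin need not be minimal, and a large phase shift could change it. A reader might infer that morning saliva cannot show any effect, or that the expected signal is near zero whatever the filters do. The document supports neither: it gives no concentrations, assay limit or effect size, and minimal is not zero. Even so, samples confined to one three-hour window cannot separate a change of phase from a change of amplitude, so desynchronised patients make the result harder to read.

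**The night-time target is inferred.** This is correct. The primary outcome says only hormone release, and the goggles are also worn in daytime. The inference rests on the Discussion, the stated purpose of the goggles and the circadian hypothesis.

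**Other data bear on circadian timing.** Sleep diaries record bed and wake times, and the morningness hypothesis is not tied to melatonin alone. However, Table 1 gives controls no diary during the intervention.

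**Conclusion.** The point holds as a matter of fit between measurement and purpose: morning saliva is poorly placed to show night-time melatonin secretion, its suppression by light, or a circadian shift. A null filter-versus-control result on this outcome would be hard to interpret. The untimed pair of samples needs reconciling with the morning window in any case.

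The size can be stated only as coverage: 12.5% of the day, and no stated evening or night time. A reader might multiply the five saliva visits by two samples and conclude that ten samples per patient all fall in the trough. The document does not say that two are taken at each visit, so that count is not established.

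The problem is confined to melatonin. Salivary and hair cortisol, α-amylase and the two sleep questionnaires are not affected. The conclusion assumes that the 9:00 to noon rule is meant to apply to the trial saliva and that the melatonin outcome is meant to reflect the night-time effect described in the Discussion.

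**What to change.** 1. In Laboratory Assessment, limit the 9:00 to noon rule to cortisol and α-amylase.
2. State the clock time of both saliva samples. Make one an evening sample at a fixed time for each patient, the same at baseline and follow-up, before the melatonin intake window opens at 21:30, with the actual time recorded.
3. Collect it under the patient's usual evening light and assigned filter use. Do not require dim light, because that would remove the exposure the filters are meant to block.
4. Define the primary melatonin outcome as the change from baseline in this evening value.

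**Cost.** The trial has not started, so this is protocol wording plus a take-home tube and instructions, with no increase in the planned number of samples. Home collection is less controlled and loses the same-room, temperature and humidity conditions. Only one of the two samples remains for morning cortisol and α-amylase. One evening value cannot separate phase from amplitude, so it should not be presented as a test of phase.

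**Fallback.** If no evening sample is taken, move morning salivary melatonin out of the primary outcomes and base no conclusion about circadian shift on it. This costs wording only.

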### Significance/Impact of the Study

RP is accompanied by significant disability, greater dependency, and a decrease in the health-related quality of life, with increased rates of admission to institutional facilities [68-70]. It is also considered a public health issue and a primary cause of headaches, sleep disturbances, and increased rates of depression [71]. Patients with RP also face difficulties in performing daily activities and increased risk of cardiovascular, metabolic, and psychiatric disorders [68-70]. Productivity losses for patients with visual impairment are likely to be amplified in patients with RP because of the early age at onset, vision challenges at school, and loss of visual function without some type of rehabilitation during prime working years [68-70].

The annual cost of adult vision problems for the National Health Service (NHS) is around US $51.4 billion. Among adults with retinal diseases, the annual total health care costs were estimated to be US $7317 higher per patient with RP, increasing the community costs by around 2.5 times because of the number of years of blindness experienced [72].

SWL-blocking filters and OM have been playing an important role in the treatment of several kinds of retinal conditions and sleep disabilities [42,43,47,60,61,73]. Unlike other expensive treatments for sleep disorders, anxiety, and depression, SWL-blocking filters or OM may provide effective control of the human circadian clock through changes in the HPA axis or the retinal–SCN–pineal axis, which could be positively correlated with improvement in the quality of life and visual function disability.

Some studies suggest a multidisciplinary treatment program that includes specialists from different areas of expertise [74]. This program provides a combination of drug treatment and SWL-blocking filters with an adequate assessment of the grade of severity (via clinical assessment) and biochemical stress (by analyzing biomarkers) and determines the impact of psychological factors on patients with RP. It could be considered a good alternative for patients with moderate and severe RP who have not benefited from expensive therapies (eg, bionic eye or genetic therapy) individually. Therefore, in this study, we suggest mimicking a multidisciplinary treatment by combining treatments and analyzing the impact of biochemical and psychological factors on anxiety and sleep disability.

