**Figure 1 figure1:**
[figure not shown]
Flow diagram illustrating the study protocol. At the allocation to interventions, the number of patients who receive the intervention will be registered, as well as those who do not receive it (together with the reason it was not applied) and those who get lost in the follow-up or discontinue the intervention. In addition, unbearable side effects and SUSARs would be appropriately notified and registered. e: patients excluded; r: randomized patients; RP: retinitis pigmentosa; SUSAR: suspected unexpected serious adverse reaction; SWL: short-wavelength light; VA: visual acuity.

**Table 1 table1:** Protocols of the intervention.

Group	Preintervention period (2 weeks)	Intervention period (30 days)
SWL^a^: optical SWL filters	Sleep diary	Sleep diary, goggles
OM^b^	Sleep diary	Sleep diary, OM
SWL+OM: optical SWL filters and OM	Sleep diary	Sleep diary, goggles, OM
Control: no intervention	Sleep diary	None

^a^SWL: short-wavelength light.

^b^OM: oral melatonin.

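### A 9:00-to-noon clock window leaves salivary cortisol loose relative to waking: it adds avoidable noise, and a shift in wake time could not be told apart from reduced stress

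*Protocol article*

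**What the plan says.** Laboratory Assessment gives the only timing rule for saliva: collection "between 9:00 A.M. and noon to minimize potential errors associated with diurnal variations". It also has temperature and humidity recorded, and menstrual phase considered for women. The section stands under screening, but no other time rule is given for the saliva samples that Table 3 schedules at V0, V1, V2, V3 and V4. The section on salivary markers asks for two samples within 24 hours and does not place them relative to waking.

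The Discussion (Summary of Findings) describes cortisol as "exhibiting a predictable peak in the morning, with a typically sharp elevation 30 minutes to an hour after awakening". For α-amylase it says only: "As with melatonin and cortisol, sAA production exhibits a regular circadian pattern".

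The hypothesis in Background and Rationale includes that the interventions will "shift their circadian rhythm to morningness". Primary Outcome Measures lists change in "hormone release (sAA, cortisol, and melatonin levels in salivary and hair samples"), and Significance/Impact of the Study describes the markers as "biochemical stress (by analyzing biomarkers").

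Wake time is an item of the sleep diary. Table 1 gives the control row as "Control: no intervention Sleep diary None", meaning a diary before the intervention and nothing during it.

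**The concern.** By the plan's own account of cortisol, time since awakening matters. A clock window does not hold that constant, either between patients or between one patient's visits. The trial studies patients with sleep disorders and tests interventions chosen partly for their effect on the circadian clock, so wake time is a variable that could well move, and move differently by arm.

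Two things are at stake for salivary cortisol. First, loose timing adds variance to change scores in a trial with 12 evaluable patients per arm. Second, if waking moves earlier under treatment, the same clock time falls later in the post-awakening course. A lower value could then reflect a shifted rhythm, a smaller hormone output, or both. The plan treats the marker as a measure of stress, and the data it schedules would not separate these explanations in the comparison with controls.

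**Working it through.** The plan states no figure on this point, so there is none to reproduce. Its sample size is used below only as a scale: a two-sided two-sample t-test with d = 1.2, 12 per arm and α = 5% gives 80.2% power, against the stated 80.02%.

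Inputs from the document: a 3-hour window (Laboratory Assessment); saliva at V0 to V4 (Table 3); a cortisol rise 30 to 60 minutes after awakening (Summary of Findings); 12 per group and d = 1.2 (Sample Size Calculation).

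Assumptions, none of them in the document: cortisol falls by r = 10% to 20% per hour after its peak (30% as a wide bound); wake time moves 0.5 to 1.5 h earlier; the SD of log change without timing noise is 0.4 to 0.8; collection times are uniform in the window and independent between visits.

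1. **What the window allows.** A patient who wakes at 8:30 and is sampled at 9:00 is 0.5 h after waking. One who wakes at 6:00 and is sampled at noon is 6 h after waking. Both comply.
2. **Extremes of the window, same wake time.** On the post-peak decline the difference is 1 − (1 − r)³: 1 − 0.9³ = 27% and 1 − 0.8³ = 49%.
3. **Noise in a change score.** The SD of a uniform 3-h window is 3/√12 = 0.866 h. For the difference of two visits it is √2 × 0.866 = 1.22 h. The slope per hour is −ln(0.9) = 0.105 or −ln(0.8) = 0.223 log units. The added SD is 1.22 × 0.105 = 0.13 to 1.22 × 0.223 = 0.27 log units, a factor of 1.14 to 1.31. If both samples at each visit fall in the window at independent times and are averaged, this drops by √2 to about 0.09 to 0.19.
4. **Effect on power, as a scale.** With SD 0.4 and r = 20%, the total SD is √(0.4² + 0.273²) = 0.484, d becomes 1.2 × 0.4/0.484 = 0.99, and power is 64%. With SD 0.8 and r = 10%, the total SD is 0.810, d is 1.19, and power is 79%. The wide bound (r = 30%, SD 0.4) gives 48%.
5. **Effect of earlier waking at an unchanged clock time.** The fall is 1 − (1 − r)^s for a shift of s hours. For s = 1 it is 10% to 20%. Over the wide ranges it runs from 1 − 0.9^0.5 = 5% to 1 − 0.7^1.5 = 41%. In SD units it is −s·ln(1 − r)/SD. The mid case (20% per hour, 1 h, SD 0.6) gives 0.223/0.6 = 0.37 SD, and with 12 per arm about a 14% chance of a significant result from the shift alone. The full range is 0.07 to 1.34 SD, or about 5% to 88%.
6. **Could the diary separate the two?** The Sleep Diary section speaks of patients in general, before and during the intervention. The more specific text excludes controls: the Overview requires diaries during the intervention from the three active groups, Table 1 shows none for controls, and No Intervention limits controls to one 2-week period. Whether those two weeks come before the start (Table 1) or after it (No Intervention), V4 is not covered.

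**The case against.** The strongest reply is that a phase shift is part of the hypothesis. The introduction says melatonin can entrain cortisol rhythms, and the outcome is worded as hormone release, so a change at fixed clock time is not simply spurious. That stands. What remains is narrower: phase and amount cannot be separated, although the marker is treated as stress.

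A restricted morning window does reduce diurnal variation, and per-patient booking rules may sit in a fuller protocol or laboratory manual. That is fair as far as the missing booking rule goes. It does not answer the stated rationale, which conflicts with the plan's own description of cortisol, or the stated absence of a control diary, which is a design choice and not an omission of the article.

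The active arms do keep diaries, so comparisons among them have wake times. Hair cortisol is also primary and does not depend on time of day, although at 1 cm per month only about a third of a 3-cm lock at V4 reflects the 30-day intervention.

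A reader might infer that cortisol and α-amylase will both be biased in favour of treatment. The documents do not support this. The awakening link is given for cortisol only. The Discussion says high cortisol tends to go with low α-amylase, so the latter might move the other way. Even for cortisol, a sample taken soon after waking may lie on the rise and not on the decline. A reader might also infer that time since waking belongs in the primary model, or that sampling should be anchored to waking. Wake time after randomisation may itself respond to treatment, so adjusting for it could remove or distort the effect. Wake-anchored booking would let the clock time of melatonin, assayed from the same saliva, drift by arm.

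**Conclusion.** The point holds for salivary cortisol, as a design weakness that should be repaired and not as a demonstrated bias. Free placement in the window adds avoidable noise, about 0.13 to 0.27 log units per change score for single samples at an assumed fall of 10% to 20% per hour. If treatment moves waking earlier, a fall could appear without any change in hormone output, and the comparison with controls could not identify its cause. The noise comes from the width of the window; the ambiguity comes from tying samples to the clock with no wake time recorded. The decline rate, the wake shift and the SD are all assumed, so the size is uncertain and may be small. For α-amylase the document supports only a circadian pattern, and hair cortisol is unaffected.

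**What to change.** - In Laboratory Assessment, book each patient's morning saliva at the same clock time (±30 minutes) at V0 to V4, inside the existing window. On the same assumptions, the timing SD of a change falls to √2 × 1/√12 = 0.41 h and the noise to about 0.04 to 0.09 log units, a third of its former size.
- Record wake time and collection time at every saliva visit in all four arms, controls included.
- Under Statistics, keep the mixed model as primary without a wake-time covariate measured after randomisation. Add a sensitivity analysis of salivary cortisol by time since awakening, labelled as conditioning on a variable that treatment may change.
- State that a fall in salivary cortisol will not be read as reduced stress unless it persists in that analysis or is supported by hair cortisol.

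The cost is slightly tighter booking, two recorded times per sample and one extra analysis. No samples or visits are added. The trial has not started, so the change is easy now, whereas unrecorded wake times could not be recovered later.
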